### Outcome measures

To achieve our primary objective of understanding how to most effectively implement oxygen systems, our mixed-methods evaluation will assess effectiveness, process and fidelity and measure a range of clinical, quality of care, technical, and health systems outcomes (including cost, sustainability, and managerial/policy implications) (Table 4).

**Table 4 Tab4:** Outcome measures used to evaluate the Nigeria Oxygen Implementation Project with associated research question and data source

Category	Research question(s)	Outcome measures	Data source
Clinical effectiveness	Does the intervention improve outcomes for the target population (specifically child pneumonia, pre-term/small neonates)?	Under-five case fatality rate (all-cause) Under-five pneumonia case fatality rate Neonatal case fatality rate Pre-term/small neonatal case fatality rate	Case notes
Epidemiological	What are the characteristics of patients with hypoxaemia in these hospitals?	Mean duration of hypoxaemia, oxygen therapy Descriptive statistics regarding hypoxaemia and oxygen therapy (age, condition, illness severity, etc.)	Case notes
Quality of care – oxygen practices	Can healthcare works correctly identify, treat, and monitor children and neonates who need oxygen therapy? Does the intervention improve healthcare workers’ oxygen care practices? How is the intervention adopted by healthcare workers? What training and supervisions is required to change practice?	Proportion of hypoxaemic children who correctly received oxygen therapy Proportion of admitted children who have pulse oximetry done correctly during admission Proportion of children receiving oxygen who had a documented clinical indication for oxygen Mean quality of care score for oxygen therapy Mean knowledge/skill scores Attitudes, behaviours, and feedback from healthcare workers (qualitative)	Case notes Knowledge/skill test Interviews/focus groups
Quality of care – broader care	What is the quality of inpatient paediatric hospital care? Does the intervention improve healthcare workers’ broader care practices?	Mean quality of care score for target conditions (pneumonia, malaria, pre-term/small neonate) Proportion of admitted children discharged against medical advice Mean length of stay Healthcare worker motivation, satisfaction Structural and process determinants of care quality (medical supplies, hygiene, guidelines, clinical review meetings, record keeping, etc.)	Case notes Interviews
Technical	Can hospital staff reliably maintain the oxygen equipment in working order? What technical problems are reported, how common, what solution, what cost?	Proportion of oxygen concentrators clean and in working order (producing > 85% oxygen, adequate flow, etc.) Proportion of pulse oximeters clean and in working order Proportion of time when concentrators were not functional, or not available for use (and reasons for non-availability) Proportion of solar power (or other improved power) systems in working order (and reasons for failure) Proportion of maintenance checks actually completed Descriptive statistics regarding technical problems identified, solutions, and costs	Technician log book (includes Standardised Report Form)
Fidelity	Was the intervention implemented as planned?	Actual timing of intervention vs intended (including training, installation, and supervision activities) Actual composition of intervention vs intended (including training, installation, and supervision activities)	Administrative records Technician log book
Cost	What is the cost of the intervention?	Equipment and installation costs Training and supervision costs Mean cost per life saved Mean cost per disability-adjusted life year (DALY) saved	Administrative records Case notes
Managerial and policy	Can the intervention be integrated in hospital managerial and state policy structures?	Hospital implementation of oxygen financing recommendations Hospital implementation of ‘oxygen team’ structure State commitment and funding for oxygen programme National impact on oxygen policy and guidelines AFASS (Acceptability, Feasibility, Affordability, Sustainability, Safety) Unintended effects Barriers and enablers	Administrative records Interviews
Sustainability	Can the intervention be sustained in the medium to long term?	Assess at 1, 2 and 5 years (using indicators above): • Technical function and maintenance processes • Healthcare worker oxygen practices • Cost recovery and ongoing financing • Hospital-level scale-up • Managerial and policy integration and scale-up	Technician log book Interviews

Case fatality rate = proportion of admitted population that die in hospital or are discharged unwell expected to die. Quality of care composite measures derived from WHO hospital care for children guidelines

### Clinical outcomes

We will collect data on clinical outcomes from case notes to evaluate clinical effectiveness and to enable exploration of variability of effect between hospitals. The primary clinical outcome will be in-hospital case fatality rates for the target population. Secondary clinical outcomes will include a range of quality of care measures relating to oxygen therapy, and supportive care. We will assess quality of care based on key clinical activities at various stages of care (assessment, diagnosis/classification, management, monitoring) based on WHO guidelines for the hospital care for children [35]. This approach is similar to the recently described Paediatric Admission Quality of Care (PAQC) score [36].

### Implementation outcomes

Our broader approach for evaluating the Nigeria Oxygen Implementation Project is guided by recommendations on the evaluation of complex interventions, particularly the theory-based realist evaluation approach [37–43]. Our programme theory articulates a series of ‘mechanisms’ through which particular parts of our intervention will impact on clinical outcomes. As such, our evaluation seeks to answer three broad questions. First, was the intervention implemented as we intended? Second, did the intervention affect the identified mechanism as we expected? Third, did the mechanisms activated by the intervention result in change clinical outcomes?

We will collect quantitative and qualitative data to answer these implementation questions. The outcome measures are described in Table 4, together with the corresponding research question and data source. The timeline of data collection is illustrated in Fig. 1.

### Sample size

We made sample size and power estimates using the Stata menu-driven programme *steppedwedge*, which is based on the Hussey and Hughes’ method for calculating sample size for a stepped-wedge trial [44, 45]. We based our assumptions on admission, prevalence, and case-fatality rate data from our needs-analysis, and informed by correlation estimates from previous studies [46]. We estimated that we would enrol approximately 16,770 children and 7670 neonates (1290 preterm) over the course of the study. Based on an alpha of 5%, we calculated that we would have approximately 80% power to detect a 35% reduction in pneumonia case fatality rate (6.1% to 4%), and 90% power to detect a 20% reduction in neonatal case fatality rate (8.2% to 6.6%). We would have greater than 90% power to detect 10% change in quality of care scores.

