As expected, different hospitals have taken slightly different approaches to particular aspects of the intervention. For example, while hospital administrators have been open to alternative financing structures for oxygen, the actual implementation of this has been difficult in some hospitals due to administrative and governance requirements. We have been impressed with the ingenuity and problem-solving capacity of the participating hospitals, but informal feedback shows significant variability in the functioning of teams at different hospitals. This highlights the importance of measuring and reporting fidelity and other process indicators, in order to better understand this variability and how improved oxygen systems work in different contexts. Overall, the intervention appears to be achieving very high levels of fidelity, and early data shows large improvements in oxygen-related clinical behaviours (e.g. the use of pulse oximetry, administration of oxygen to hypoxaemic patients, etc.). Interim safety data suggests that the intervention is not causing harm and probably causing benefit, and we anticipate having adequate power to detect a meaningful difference by the end of data collection despite lower than expected admission numbers.

Oxygen therapy is a basic, life-saving therapy that is relevant for many paediatric and adult health conditions, but has limited global availability. Our study should provide quality evidence on the effectiveness of improved oxygen systems, and how to better implement and scale up oxygen systems in resource-limited settings. Our results will have important implications for policy-makers, hospital administrators, and child health organisations in Africa and globally. Our findings may have broader applicability to other healthcare interventions that are worthy of scale-up but are proving challenging to implement in the places that can benefit the most.

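### The stated 90% power for neonatal case fatality does not follow from the stated design, which gives about 30% and at most about 41%; the 80% for pneumonia cannot be checked

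*Protocol article*

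**What the plan says.** The Sample size section of the protocol article names a Stata program "which is based on the Hussey and Hughes’ method for calculating sample size for a stepped-wedge trial". It expects "approximately 16,770 children and 7670 neonates (1290 preterm) over the course of the study". The test level is given as "Based on an alpha of 5" per cent, without saying whether one- or two-sided. Two power claims follow, one for each primary outcome named in the abstract:

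- Neonates: "90% power to detect a 20% reduction in neonatal case fatality rate (8.2% to 6.6" per cent.
- Pneumonia: "approximately 80% power to detect a 35% reduction in pneumonia case fatality rate (6.1% to 4" per cent.

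The inputs are described only in general terms: "We based our assumptions on admission, prevalence, and case-fatality rate data from our needs-analysis", and "informed by correlation estimates from previous studies". The section gives no ICC value and no expected number of pneumonia cases; the Study design section says only that a moderate ICC was anticipated.

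Table 1 and the Allocation section fix the design: 12 hospitals, 6 periods of 4 months, all control in period 1, three hospitals crossing at each of steps 2, 3, 4 and 5, and all on intervention in periods 5 and 6. The analysis section adjusts for calendar time and clustering.

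The Discussion later says "we anticipate having adequate power to detect a meaningful difference by the end of data collection despite lower than expected admission numbers".

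**The concern.** An absolute difference of 1.6 percentage points on a base of 8.2% is small for 7670 patients even in a simple two-arm trial. A stepped wedge that also estimates period effects will normally need more patients than that, unless the ICC is very high. A claim of 90% power therefore looked too favourable.

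The neonatal outcome is one of two primary outcomes. If readers believe the trial had 90% power for a 20% reduction, they will take a non-significant neonatal result as evidence against such an effect. If the true power is nearer 30%, that reading is unsafe. The Discussion's reassurance, made when admissions were already below plan, adds to the risk.

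**Working it through.** **Inputs from the article.** Hospitals I = 12; periods T = 6; exposed periods per hospital 5, 4, 3 and 2 in the four groups of three; N = 7670 neonates; rates 8.2% and 6.6%; alpha 5%. The stated relative reduction is consistent: 1.6/8.2 = 19.5%.

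**Assumptions.** Two-sided test (one-sided also shown), equal cell sizes, normal approximation, ICC varied because none is stated.

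**Benchmark: individual 1:1 randomisation, no clustering, no period effects.**
SE = sqrt[(0.082×0.918 + 0.066×0.934)/3835] = 0.00598; z = 0.016/0.00598 = 2.68; power = Φ(2.68 − 1.96) = 76% (85% one-sided). For 90%, 11,248 neonates would be needed.

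**Hussey-Hughes variance for the stated design.**
With U the total number of exposed cells, W the sum of squared column totals and V the sum of squared row totals:

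Var = I·s·(s + T·τ²) / [(I·U − W)·s + (U² + I·T·U − T·W − I·V)·τ²],

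where s is the within-hospital variance divided by the cell size m, and τ² is the between-hospital variance.

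- U = 3×(5+4+3+2) = 42
- W = 0² + 3² + 6² + 9² + 12² + 12² = 414
- V = 3×(25+16+9+4) = 162
- I·U − W = 504 − 414 = 90
- U² + I·T·U − T·W − I·V = 1764 + 3024 − 2484 − 1944 = 360
- m = 7670/72 = 106.5
- Mean binomial variance = (0.082×0.918 + 0.066×0.934)/2 = 0.06846

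*ICC 0:* s = 0.06846/106.5 = 0.000643; Var = 12×0.000643/90 = 0.0000857; SE = 0.00926; z = 1.73; power 41%.

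*ICC 0.01:* τ² = 0.000685; s = 0.99×0.06846/106.5 = 0.000636; Var = 0.0000362/0.3037 = 0.000119; SE = 0.0109; z = 1.47; power 31%.

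| ICC | Power, two-sided | Power, one-sided | Neonates for 90% (two-sided) |
|---|---|---|---|
| 0 | 41% | 53% | 26,975 |
| 0.001 | 36% | 49% | 35,928 |
| 0.01 | 31% | 43% | 39,481 |
| 0.05 | 31% | 43% | 38,326 |
| 0.10 | 32% | 44% | 36,363 |
| 0.20 | 35% | 47% | 32,346 |

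The table holds the total variance fixed. Fixing the within-hospital variance instead lowers power slightly, to 29% at ICC 0.1 to 0.2, and raises the number for 90% to about 40,400.

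**Attempts to recover 90%.** None of these does so:

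- five periods instead of six, ICC 0 to 0.2: 33-47%;
- the unequal hospital sizes of Table 2: 29-40% on average;
- twice Table 2's annual 5076 neonates, i.e. 10,152: 38-51%;
- a very high ICC: with total variance fixed, 90% is reached only at an ICC of about 0.81.

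**Detectable effect.** Solving the same formula for 80% power with 7670 neonates gives a relative reduction of about 31% at ICC 0 and about 36% at ICC 0.01 to 0.05.

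**Pneumonia.** The relative reduction is again consistent: 2.1/6.1 = 34%. The number of cases is not stated, so the power cannot be reproduced. Solving for 80% power instead gives 8,174 cases at ICC 0 (8,174/16,770 = 49% of children), and about 11,000 to 12,200 cases at ICC 0.005 to 0.10 over the two variance conventions (66-73%). If pneumonia made up 20% of the 16,770 children, power would be 32-43%; at 30% it would be 44-59% (ICC 0 to 0.05). These shares are illustrations, not figures from the article.

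**The case against.** The strongest defence is that the article condenses a fuller protocol. The ICC, the sidedness of the test and the pneumonia count may all be recorded there, and a result near 30% depends on an assumed ICC. This is fair as to precision: the neonatal figure should be given as a range, about 29-41% two-sided or 41-53% one-sided. It does not rescue the 90%, because every other neonatal input is stated and no ICC from 0 to 0.2 comes near it.

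The defence succeeds for pneumonia. A reader might infer that the 80% is equally impossible, that both primary outcomes are underpowered, or that the whole trial had a one-in-three chance of detecting its targets. The documents do not support this. The required 8,200 to 12,200 cases is below the 16,770 children expected. Such a share looks unlikely for all-cause admissions aged 28 days to under 18 years, particularly as Table 4 counts only under-five pneumonia, but nothing in the article excludes it.

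A reader might also guess the cause: the whole-trial size per hospital, 7670/12 = 639, entered as the size of each hospital-period gives 93-95% at ICC 0.005 to 0.05. That is close to 90%, but nothing in the article says it was done, and the finding does not depend on it.

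Finally, the Discussion speaks of a meaningful difference without naming an effect size or a power. It is a general expectation, not a second arithmetic error.

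**Conclusion.** The neonatal claim is wrong under the article's own method and inputs. Power for 8.2% to 6.6% with 7670 neonates is about 30% at ICC 0.01 to 0.05 and at most about 41% at any ICC from 0 to 0.2, against the stated 90%. This rests on a two-sided 5% test, equal cell sizes and the normal approximation; relaxing the first two does not change the conclusion. The individually randomised 76% is a benchmark rather than a strict ceiling, since an extremely high ICC could in principle exceed it, but such an ICC is not the moderate one anticipated.

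The pneumonia claim is unverified, not refuted. It needs its case count and ICC before it can be relied on. The error in a stated primary-outcome power figure must be corrected, and the neonatal part alone is enough to require it.

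**What to change.** Re-run the calculation with the size per hospital-period (7670/72, about 107 neonates) and a stated ICC and test sidedness. Replace the neonatal 90% with the resulting power, or with the reduction detectable at 80% power. State the expected number of pneumonia cases and recheck the 80% against it. Then revise the Discussion sentence on adequate power to agree with the corrected figures and with the lower admissions.

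The cost is one re-run and a few restated figures. No extra patients and no change of design are needed; the only downside is a less favourable stated power. Recruitment is still under way according to the Trial status section, so this can be done before the results are read.

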### Allocation

We used pre-randomisation stratification to ensure each step included one ‘large’ (>1500 child admissions per year) and two ‘small/medium’ hospitals (<1500 admissions), as we supposed that the size of hospital (and associated staffing and expertise) may influence the outcomes. We randomised hospitals to receive the intervention in steps 2, 3, 4, or 5, using a computer-generated random sequence generator, resulting in one ‘large’ and two ‘small’ hospitals allocated to receive the intervention at equally spaced 4-month intervals. This stepped-wedge randomised design enabled all hospitals to receive the intervention, while maintaining a robust controlled design (individual hospitals acting as their own historical control, and each other’s contemporaneous control).

We conducted randomisation with four members of the research team in attendance, and shared the randomisation order with hospitals as part of the participatory planning process. It was not possible to blind patients, healthcare-providers, or hospital administrators from the intervention due to the nature of the intervention.

### Data management and analysis

Clinical data will be collected from individual case notes by trained nurse data collectors. These data collectors will complete standardised Case Report Forms (CRF1) (see Additional file 2), which will be collated and returned to the project manager before being handed to the data manager. Trained data-entry clerks will double-enter the data into EpiData (EpiData Association, Odense, Denmark). The data manager will supervise the data entry and verification process, and will export the raw data file into.dta format for analysis using Stata v14 (StataCorp, College Station, TX, USA). All data will be de-identified before analysis to preserve confidentiality. The primary investigators will have full access to the data, and summary data will be made available for external validation purposes.

We will report characteristics of the individuals and clusters descriptively to illustrate potential imbalance between exposed and unexposed and allow for discussion of potential biases. We will illustrate the number of observations within each cluster by overlaying the summary numbers onto a stepped-wedge diagram. We will analyse effectiveness using intention-to-treat, according to the time hospitals were randomised to crossover. We will report any differences between intended crossover time and actual crossover time. We will adjust for the effect of calendar time, clustering, and other significant confounders using generalised linear mixed models (GLMM) or generalised estimating equations (GEE) [32, 44]. We will examine heterogeneity in effects between different hospitals using within-cluster comparisons of exposed and unexposed periods. This will contribute to better understanding of how various contextual factors influence effectiveness. We will conduct 6-monthly reviews of data for presentation to a supervisory committee, and to ensure that there is no evidence of significant unintended harm. Given the anticipated benefits and safety of this intervention, we do not have a formal data monitoring committee.

Equipment data will be collected by trained biomedical technicians during routine preventive maintenance visits. These technicians will complete standardised Case Report Forms (CRF2), and return them to the project manager. They will be entered and verified using the same procedures as for CRF1. We will report equipment outcome data descriptively, allowing for comparison between different hospitals.

Healthcare worker knowledge will be assessed using individual written tests (TEST) before and after each training, and at 6-month periods post implementation. Trainers will administer these tests, collate the completed tests, and return them to the project manager. They will be entered and verified using the same procedures as for CRF1. We will report before and after test scores in relation to the basic pulse oximetry training, full oxygen training, and at follow-up. We will report confidence intervals for all estimates, and assess for statistical significance using a *t* test for (normally distributed) continuous outcomes, and chi-squared for binary outcomes.

Qualitative data from interviews and focus groups will be transcribed and verified for accuracy by participants. We will import these to NVivo v11 (QSR International, Doncaster, VIC, Australia) for data management and analysis. We will use the qualitative data to explore the reasons behind the observed intervention effects (the ‘mechanisms’) and variation between hospitals (the contextual influences). To achieve this we will use a Grounded Theory approach to data analysis, using mixed inductive and deductive content analysis approaches.

Other process data will be collected from administrative records, finance ledgers, and correspondence between investigators and hospitals. We will use this data to understand how the intervention was implemented, identify new avenues of inquiry, and collate practical lessons for future application.

We will report results using the CONSORT 2010 extension to cluster randomised trials, with modifications for the stepped-wedge design as proposed by Hemming et al. [32]. We will publish our results in an open-access journal.

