## Methods/design

### Study design

This is a stepped-wedge cluster randomised field trial (cross-sectional). The study design and characteristics are summarised in Table 1 and Fig. 1 (see Additional file 1 for the Standard Protocol Items: Recommendations for Interventional Trials (SPIRIT) Checklist).

**Table 1 Tab1:** Characteristics of the Nigeria Oxygen Implementation Project stepped-wedge cluster randomised trial

Trial characteristic	Definition
Cluster unit	Individual hospital. There are 12 clusters (hospitals)
Cluster randomisation	3 clusters (hospitals) randomised to receive the intervention at a particular time point. There are 4 cluster groups
Length of steps (observation periods)	4 months
Number of steps	6 steps
Description of steps	Step 1 – all hospitals are pre-intervention Steps 2, 3, 4 – intervention clusters are added sequentially Steps 5, 6 – all hospitals are intervention hospitals
Duration of trial	24 months
Pre-intervention period	4 to 16 months
Post-intervention period	8 to 20 months

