Standardised equipment package oxygen concentrator pulse oximeter oxygen delivery equipment maintenance gear	To enable reliable, continuous access to oxygen for all children and neonates To make it easy to use oxygen correctly To make it easy to maintain oxygen equipment in good function	Selection of quality, user-friendly equipment that is proven to function in hot, humid environments and capable of being maintained with minimal technical skill: Airsep Newlife Elite oxygen concentrator, Lifebox pulse oximeter (neonatal and child probes), Airsep Sureflow flowmeter assembly, nasal prongs and tubing, oxygen analyser, installation and maintenance gear
Clinical education and support basic oximetry training healthcare worker training on the clinical use of oxygen supportive supervision	To build healthcare worker capacity and motivation to use oxygen well To stimulate healthcare workers to make their work environment more conducive to good clinical care	Clinical training material based on WHO guidelines [35, 48] and will include: clinical approaches to sick children; recognition and treatment of hypoxia; use of pulse oximetry and concentrators. Using Merrill’s approach to active learning [31], training will be active, task-based, and intentionally target motivation. Training conducted on-site at participating hospitals. One-hour basic pulse oximetry training for nurses and physicians when pulse oximeters are distributed. Half-day training on the clinical use of oxygen at the time of installation, using an ‘apprentice’ model where individual leaders are trained first, and then they are supervised to train their colleagues (and coordinate future re-training)
Technical training and support technician training on maintenance and repair supportive supervision	To build technician capacity and motivation to maintain and repair equipment To stimulate technicians to modify their procedures to make equipment care easier	Technical training material adapted from previous projects [12, 14, 15] and delivered by an expert biomedical engineer. Three-day training conducted at a central location for central engineers and at least one technician from each participating hospital. Regular supervision visits (at least 3 monthly) for re-training, review and feedback, and to identify areas needing additional attention

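### The planned tests of knowledge scores ignore the grouping of staff in 12 hospitals, and chi-squared also ignores repeat testing, so intervals and p-values for this secondary outcome are likely to be miscalibrated

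*Protocol article*

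**What the plan says.** The knowledge data have their own paragraph under Data management and analysis in the protocol article. The measurement schedule is: "Healthcare worker knowledge will be assessed using individual written tests (TEST) before and after each training, and at 6-month periods post implementation". The comparison is: "We will report before and after test scores in relation to the basic pulse oximetry training, full oxygen training, and at follow-up". Every estimate is to carry a confidence interval, and significance is to be judged by a t test or, for binary results, by chi-squared: "test for (normally distributed) continuous outcomes, and chi-squared for binary outcomes". The paragraph mentions neither pairing nor hospital.

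The preceding text, on clinical data, takes a different approach: "We will adjust for the effect of calendar time, clustering, and other significant confounders using generalised linear mixed models (GLMM) or generalised estimating equations (GEE"). It describes the effectiveness analysis by randomised crossover time.

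Table 1 defines the cluster: "Individual hospital. There are 12 clusters (hospitals"). Table 3 says of the clinical training: "Training conducted on-site at participating hospitals". Table 4 lists "Mean knowledge/skill scores" among the outcomes for oxygen practices, under quality of care.

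**The concern.** The knowledge data have two kinds of dependence.

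- **Within person.** A before and an after test around one training session are naturally taken by the same individual. Ordinary chi-squared treats the two sets of results as coming from different people. A t test does the same unless it is paired.
- **Within hospital.** Training is given at each site, and Table 3 has local leaders trained first, who then train their colleagues under supervision. Staff of one hospital therefore share a trainer and a setting. The Discussion also reports, from informal feedback, that team functioning differs markedly between hospitals. Even a paired t test treats those colleagues as independent.

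The evaluation asks whether the intervention moved the mechanisms it was meant to move, and knowledge scores are one of the quantitative measures bearing on that. The plan promises confidence intervals and significance tests for them. If the intervals have the wrong width, the training effect will look more or less certain than it is.

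**Working it through.** The protocol article gives no sample size, standard deviation, correlation or power for the knowledge test, so there is no planned figure to reproduce. What follows is a sensitivity check on assumed correlations.

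**Inputs**
- Hospitals: 12 (Table 1).
- Paediatric nurses (Table 2, leading figure where a second stands in brackets): 11 + 7 + 18 + 26 + 31 + 62 + 26 + 33 + 9 + 4 + 18 + 16 = 261. The mean is 261/12 = 21.75, about 22. These counts stand in for test takers, whose number is not given.
- Size-weighted mean, which allows for unequal hospitals: sum of squares / sum = 8417/261 = 32.2.
- Assumed: before/after correlation r of 0.3 to 0.7; ICC of the change score of 0 to 0.20; two-sided 5% level.

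**1. Paired t test that ignores hospital.** The standard error is too small by the factor sqrt(1 + (m − 1) × ICC).

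| Staff per hospital (m) | ICC 0.05 | ICC 0.20 |
|---|---|---|
| 5 (assumed) | sqrt(1.20) = 1.10 | sqrt(1.80) = 1.34 |
| 22 (simple mean) | sqrt(2.05) = 1.43 | sqrt(5.20) = 2.28 |
| 32.2 (size-weighted mean) | sqrt(2.56) = 1.60 | sqrt(7.25) = 2.69 |

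The true type I error is 2 × (1 − Φ(1.96/sqrt(V))), where V is the true variance divided by the variance the test assumes. With m = 32.2 it is 5.0%, 8.7%, 22%, 33% and 47% at ICC 0, 0.01, 0.05, 0.10 and 0.20.

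**2. Unpaired t test on the same staff, no hospital effect.** Here V = 1 − r. The standard error is too large by sqrt(1/(1 − r)), which is 1.20, 1.41 and 1.83 at r = 0.3, 0.5 and 0.7. The true type I error falls to 1.9%, 0.6% and 0.03%.

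**3. Unpaired t test that ignores both.** Here V = (1 − r) × (1 + (m − 1) × ICC), again with m = 32.2.
- r = 0.5, ICC 0.05: V = 0.5 × 2.56 = 1.28, error 8.3%.
- r = 0.7, ICC 0.05: V = 0.3 × 2.56 = 0.77, error 2.5%.
- r = 0.3, ICC 0.10: V = 0.7 × 4.12 = 2.89, error 25%.

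**4. Simulation.** This used 4000 runs per scenario, 12 hospitals and 261 staff, with r = 0.3, 0.5 and 0.7 and ICC = 0, 0.05 and 0.10.
- The paired and unpaired t tests came close to the formulas. For example, the paired test gave 22% to 23% at ICC 0.05.
- Chi-squared on before/after pass rates gave 0.6% to 3.0% at ICC 0, and 3.1% to 18% at ICC 0.05 to 0.10.
- A one-sample t test on the 12 hospital mean changes gave 4.4% to 5.6% in every scenario.

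**The case against.** The best defence is that the article is condensed. It names a t test without its form, and for before and after scores on individual tests a paired t test is the natural reading. Paired or not is a detail commonly left to the SAP. That stands: a reader might infer that the plan uses a two-sample t test for independent groups, but the text does not say so. It does not answer the point on clustering, because pairing leaves colleagues in one hospital independent. Nor is this only missing detail, since the paragraph names methods different from the mixed or marginal models it sets for the clinical data.

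Other limits also stand:

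- **Size.** The number tested is unknown. Leaders are trained first, so few staff per hospital may sit some tests, which shrinks the effect. Physicians also attend the oximetry training, and testing all staff would enlarge it. All correlations are assumed.
- **Follow-up.** A reader might infer that the same workers are followed at every 6-month test. The article does not say so, and Table 3 expects staff to rotate.
- **Chi-squared.** No binary knowledge endpoint is defined. The outcome in Table 4 is a mean score, so this part matters only if some item is analysed as yes/no.
- **Importance.** Knowledge scores are one process measure, listed beside case-note measures of actual oxygen practice. The same section gives the qualitative data the main part in explaining mechanisms.

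**Conclusion.** The point holds in a limited form. As written, the tests named for knowledge scores make no allowance for hospital, and chi-squared makes none for repeat tests on a person. The resulting intervals and p-values are likely to be miscalibrated.

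If the t test is paired and hospitals differ in change, the intervals are too narrow, by a factor of about 1.4 to 2.3 in the standard error at 22 staff per hospital, or 1.1 to 1.3 at 5. If it is unpaired on the same staff, the lost pairing pulls the other way and the two errors partly offset. The net direction cannot be known beforehand. These figures rest on the assumed ICC of 0.05 to 0.20, the assumed r, and nurse counts used in place of test takers.

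Two stronger readings are not supported. One is that the results will certainly be wrong: with a paired t test, a single before/after pair and no hospital variation in change, the error rate is the nominal 5%. The other is that the fault reaches the mortality comparison: the t test and chi-squared sentence sits in the knowledge-test paragraph, and the effectiveness analysis has its own adjustment for clustering.

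**What to change.** Replace the t test and chi-squared sentence with one that does the following:

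- Link tests by an anonymous staff code where possible.
- Analyse scores with a linear mixed model: test occasion as a fixed effect, worker and hospital as random effects, and small-sample degrees of freedom suited to 12 clusters. A t test on the 12 hospital mean changes serves the same purpose and is simpler. It weights hospitals equally and has 11 degrees of freedom.
- For any binary item, use a logistic model that allows for clustering in place of chi-squared.
- Where tests cannot be linked, or staff have rotated, keep test occasion and hospital clustering in the model and say how staff tested only once are handled.

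The cost is a little extra analysis work, a staff code on the test forms if there is none already, and possibly wider intervals. The trial's design, sample size and mortality analysis do not change.
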